## Abstract

There is currently no standardised self-reporting tool, or established cut-off points for comprehensive risk assessment for patients undergoing cancer surgery. This study aims to develop, validate, and implement an online self-reporting preoperative screening tool that identifies modifiable risk factors. We believe that the timely identification of high-risk patients, based on their preoperative physical, nutritional, and psychological statuses observed through a self-reporting online screening tool, would streamline identification of high-risk patients, enabling referral to targeted interventions.

## 1. Introduction

Approximately 20% of the global population will develop cancer within their lifetime, with one in twelve people developing gastrointestinal cancer, and one in sixteen cases leading to death [1,2]. Colorectal cancer represents close to one in ten cancer cases and deaths, with the second highest rates of mortality. Liver cancer has the third highest rate of mortality and is the sixth most diagnosed cancer, while stomach cancer ranks fifth for both incidence and mortality worldwide [1]. According to the global cancer statistics for 2022, gastrointestinal cancer made up 24.6% of newly diagnosed cancers and 34.2% of cancer mortality [1]. The global demographic-based predictions indicate that the annual rate of cancer will increase by approximately 77% by 2050 [1].

Despite the rising incidence and advances in medical technology, surgery remains the mainstay of curative treatment, with or without chemotherapy and/or radiotherapy for selected patients [3]. The overall survival for patients undergoing gastrointestinal cancer surgery has improved significantly over the past two decades, with five-year survival rates ranging from less than 30% to 70% depending on disease stage [4]. However, rates of postoperative complications remain high, occurring in up to 65% of patients [5,6]. The presence of postoperative complications is associated with a greater burden to the patient, increasing hospital stay, decreasing quality of life, and increasing health service costs. Recent studies have demonstrated that patients presenting with poor preoperative physical status, nutrition, and/or mental health are up to 50% more likely to develop postoperative complications, subsequently having poor postoperative outcomes [7,8,9].

To attenuate the reduced physiological and functional capacity associated with gastrointestinal cancer surgery and the impact of preoperative comorbidities, recent studies have explored the role of prehabilitation in increasing physiological reserve and functional capacity to improve patient recovery and return to baseline functioning [10]. Gastrointestinal cancer carries a known physical, nutritional, psychological, and financial burden that may be increased with repeat admissions and longer hospital stay. A systematic review and meta-analysis performed by Mizrahi et. al. determined that on average, patients who underwent exercise prehabilitation reduced their length of hospital stay by approximately 1.4 days and reduced their hospital admission when compared to a usual care control [11]. Similarly, a systematic review and meta-analysis performed by Waterland et al. found a mean reduction in hospital length of stay of 3 days in abdominal cancer patients [12]. Studies focused on lung cancer populations have demonstrated a 4-8 day reduction in hospital length of stay [13,14]. Similarly, nutritional status has been shown to influence prehabilitation responses, with malnourishment being a barrier for improved functional capacity [15]. The identification of patients that are at a high risk of postoperative complications would allow for appropriate preoperative intervention selection. The establishment of a validated preoperative online screening tool, including measures of physical, nutritional, and psychological status, would enable tailored interventions, resulting in health optimisation before surgery and benefiting patients during the recovery period. Individual studies investigating physical, nutritional, and psychological status have shown the importance of positive preoperative states for improved recovery following colorectal surgery [16,17].

Currently, the main pitfall within the preoperative workup period is that the assessment of potential modifiable risk factors, such as physical status, nutrition, and mental health, is undertaken in the preadmission clinic, which normally takes place within one to two weeks of the planned surgical procedure [18]. While a team of doctors, nurses, and other health professionals conduct a comprehensive screening and assessment of patients at the preadmission clinics, most of the identified risk factors at this stage are either non-modifiable (e.g., diabetes mellitus) or are modifiable but are not able to be effectively addressed due to the limited time between the assessment and scheduled surgical procedure (e.g., deconditioning, malnutrition). Preadmission counselling involving patient education on surgical milestones and criteria for discharge have been suggested to enhance recovery following cancer surgery, resulting in decreased length of hospital stay and complication rates [19,20]. Early evaluation of patient limitations and expectations through a screening process can enable tailored interventions that patients may be more likely to adhere to. Thus, the innovative implementation of an online, self-reporting, preoperative screening tool 4–6 weeks prior to the surgery would be beneficial in the identification of modifiable risk factors that are associated with worse postoperative outcomes [21]. This can further be utilised to allow patients and clinicians to work collaboratively towards shared goals enabling enhanced recovery outcomes [22,23]. There are several available preoperative screening tools used to individually determine the status of patients before cancer surgery, including the following: (i) physical status: the Duke Activity Status Index (DASI) and the Community Health Activities Model Program for Seniors (CHAMPS), used to assess functional capacity [10,24]; (ii) nutrition: the Patient-Generated Subjective Global Assessment-Short Form (PG-SGA-SF), Nutrition Risk Screening (NRS), and Malnutritional Universal Screening Tool (MUST) have proven their ability to identify adverse and enhance clinical outcomes in cancer patients [20,25,26]; and (iii) psychological tools: the Hospital Anxiety and Depression Scales (HADS), Kessler Psychological Distress Scale (K6), and Patient Health Questionnaire depression scale (PHQ-9) [7,27,28].

Despite the availability of these tools and the strong correlations demonstrated with gold standard objective measures, none of the identified tools take into consideration all three domains (i.e., physical, nutritional, and psychological). Currently, there is no standardised screening tool or recommended optimal cut-off point that can be used to identify individuals at higher risk of poor outcomes when undergoing gastrointestinal cancer surgery, as most studies use different tools. Therefore, the main aim of this study is to develop, test, and implement a simple, online, self-reporting, preoperative risk stratification tool that will identify modifiable physical, nutritional, and/or psychological factors to ensure patients receive targeted and tailored interventions. Hence, the specific aims of this project are to (i) develop a preoperative online tool to assess self-reported measures of physical capacity, nutrition, and mental health, using previously validated questionnaires in accordance with experts’ feedback; (ii) investigate the potential association between the preoperative online tool and postoperative surgical outcomes, including postoperative complications and length of stay, and to determine risk stratification thresholds for the preoperative online tool; and (iii) to implement the preoperative online tool in the preoperative hospital setting.

## 2. Materials and Methods

### 2.1. Study Design

This project utilises a rigorous sequential exploratory mixed-methods design, incorporated within three distinct stages (Figure 1) [29].

### 2.2. Stage 1—Development

The preoperative online screening tool will be developed according to three research streams, as below.

#### 2.2.1. Identification of Preoperative Screening Tools

##### Protocol and Registration

A scoping review will be performed according to the methodological framework proposed by Arksey and O’Malley [30], and reported according to the Preferred Reporting Items for Systematic Reviews and Meta-Analysis (PRISMA) [31,32], with the detailed review protocol published a priori on the Open Science Framework platform. The main aim of this scoping review is to identify the most up-to-date tools suitable to be used in the preoperative period to screen physical, nutritional, and/or psychological factors in surgical cancer patients.

##### Search Strategy and Eligibility

A search strategy will be created in conjunction with an experienced librarian from The University of Sydney and performed on the Medline, Embase, Evidence Based Medicine (EBM), Cumulative Index of Nursing and Allied Health Literature (CINAHL), and PsycINFO databases. A combination of the following keywords and subject headings will be used: ‘screening tools’ AND ‘gastrointestinal neoplasms’ AND ‘preoperative’ AND ‘nutrition’ OR ‘psychological’ OR ‘exercise’. The completed search strategy will be made available upon completion. The bibliographies of included studies found through the database search will also be examined. Studies published in the literature after the year 2000, written in the English language, including adult (≥18 years) patients undergoing gastrointestinal cancer surgeries and reporting on physical, nutritional, and/or psychological screening tools will be included. Gastrointestinal surgeries on the liver, stomach, spleen, pancreas, peritoneal, colon, rectum, and oesophagus will be included.

Systematic reviews and meta-analyses, randomised control trials (RCTs), retrospective and prospective cohort studies, cross-sectional studies, and case series with >10 participants undergoing gastrointestinal cancer surgery will be included. Conference abstracts will also be examined. Studies reporting screening tools on mixed populations (>80% of the sample non-cancer) or patients with any cancer not listed above will be excluded.

##### Selection and Data Collection Process

Two review authors will independently screen all the articles and extract all the data. As this is a scoping review, we are not planning to assess the quality of the identified articles. The COVIDENCE software will be used to manage the review and synthesise the results [33]. Detailed information on the identified screening tools will include screening tool name, year developed, recall period, number of items, number of domains, response options, score range, time to complete, tool availability, use in cancer surgical patients, and psychometric information. This review will provide invaluable information for the first round of Section 2.2.2. (below).

#### 2.2.2. Delphi Study

##### Study Design

The Delphi methodology will be employed for gaining consensus on the selection of the most appropriate preoperative physical, nutritional, and psychological screening tools for patients undergoing elective gastrointestinal cancer surgery. Each identified tool will be grouped by domain (physical, nutritional, and psychological) before undergoing a three-round iterative survey.

##### Participants, Recruitment, and Setting

Guidelines proposed by Hasson and Colleagues [34] and the recommendations from Conducting and REporting of DElphi Studies (CREDES) [35] will be used to establish consensus across a multidisciplinary panel of local, national, and international experts including doctors, nurses, allied health professionals, research groups, statisticians, epidemiologists, and health- and policymakers. This approach will facilitate the representation of professional groups that directly influence patient decisions and would benefit from the results of this project. For this, members of the Global (P)rehabilitation Initiative (https://source.sydney.edu.au/global-prehabilitation-initiative/ (accessed on 12 May 2024)), consisting of approximately 2000 multidisciplinary experts from 6 continents, will be approached and invited to participate. In addition, authors from the identified literature (Section 2.2.1) will also be invited to participate. The invitation letter will also ask individuals to disseminate the study invitation to their networks. Consent will be gained by all participants wanting to form part of the Delphi survey, and ethical consultation will be sought from Sydney Local Health District Human Research Ethics Committee (HREC). It is estimated that between 100 and 200 participants will form the multidisciplinary panel involved in this Delphi survey.

Demographic characteristics including age, gender, education level, role/discipline, country of practised, and involvement within prehabilitation will be collected from the expert panel. A three-step Delphi method will be employed through a secure web application (REDCap) [36].

### 2.3. Delphi Methodology

#### 2.3.1. First Round

The preoperative screening tools identified in the abovementioned scoping review (Section 2.2.1) will be compiled in the first round and distributed via email to participants. In this round, experts will have the opportunity to add extra preoperative screening tools there were not identified in the scoping review. Identified tools will be categorised based on the factors they encompass (i.e., physical, nutritional, psychological). Using a 5-point Likert Scale (1 = no importance, 2 = limited importance, 3 = neither important nor unimportant, 4 = somewhat important, 5 = critically important), determination of the appropriateness of tools can be made. Furthermore, we will be able to rate identified screening tools based on the following consensus criteria prior to Round 2 [37,38]:Consensus in: ≥ 70%of experts on the use of appropriate tools, marking them as important (≥4).Consensus out: ≥ 70%of experts on the dismissal of tools, marking them as of limited importance (≤2).No consensus: neither of the above criteria are met.

#### 2.3.2. Second Round

In Round 2, experts will be emailed an updated list of preoperative screening tools with the group scores and their individual scores. The abovementioned Likert scale will be implemented to allow for newly identified tools to be compared to the same standards previously used. Bias will be mitigated by randomisation of tools, and properties identified by 70% of participants as either important or critically important, or without consensus, will be collated for the third round.

#### 2.3.3. Third Round

Round 3 will be comprised of a final Delphi survey; using the abovementioned Likert scale, members will be encouraged to discuss the remaining preoperative screening tools until agreement is reached to retain, modify, or eliminate from the final statement. Following Round 3, a consensus on appropriate tools of ≥70% and a median score of ≥4 on the Likert scale will be used as criteria to form the online screening tool (Section 2.4). If neither criteria 1 or 2 is met at the completion of three rounds, consensus will be defined as the majority agreement [39].

#### 2.3.4. Statistical Analysis

Descriptive statistics will be employed to summarise participant characteristics. All three rounds will calculate the median scores of each identified preoperative screening tool using the 5-item Likert Scale previously described, and the inter-rater reliability (ICC) will be calculated.

### 2.4. Development of Online Screening Tool

This step will utilise the evidence acquired in Section 2.2.2 to develop a secure web application that will allow the management of the online preoperative screening tool and data collection. Original developers of the identified screening tools will be consulted regarding their use of the online screening tool. For tools that are not developed in an online survey format (i.e., solely paper-based tools or those using consultation/telephone), or not freely available, developers will be approached regarding use within this online screening tool. We will assemble a focus group including clinicians and experts, along with patients and health consumers, to determine the format of the online preoperative screening tool. This will include pilot testing to check the comprehensibility and useability of the tool. The finalised tool will be used in stage 2 below.

### 2.5. Stage 2—Testing

#### 2.5.1. Design and Setting

A prospective longitudinal cohort study will be conducted by recruiting consecutive patients undergoing elective gastrointestinal cancer surgery at several national and international hospitals over a 12-month period beginning at the completion of the Delphi survey. All patients will be required to complete the informed consent form and will be followed until 30 days post-operation. Patient data will be collected from the online screening tool and electronic medical records over this period. This study protocol was written in accordance with the STROBE statement [40].

#### 2.5.2. Recruitment

A range of national and international centres will be approached, with surgeons, anaesthetists, and clinical researchers from the participating hospitals involved in patient screening. All patients that meet our inclusion criteria will be provided with an information sheet regarding the study, and if interested in participating, a researcher from the study will contact them to discuss the study further. Clinical assessment and decision-making will proceed according to usual clinical protocols.

#### 2.5.3. Participants

All participants must satisfy the following inclusion criteria and none of the exclusion criteria:

#### 2.5.4. Inclusion Criteria

Adults (aged ≥ 18 years) of any gender;Patients who are undergoing elective curative surgery for gastrointestinal cancer including for their colon, rectum, pancreas, stomach, liver, spleen, or oesophagus;Patients with the capacity to provide informed consent;

#### 2.5.5. Exclusion Criteria

Patients who have inadequate English language skills to complete the online screening tool or are unable to be assisted with the completion of the online screening tool.

#### 2.5.6. Participant Consent

All participants will be asked to complete a written consent form after they have read the provided information sheet and have had time to consider participation. Interested participants will be provided with a secure link to the preoperative screening tool. Participants involved are under no obligation to complete the screening tools and can withdraw from the study at any time. Participants can be assured that choosing to withdraw from the study will not affect any relationships with their treating team or quality of care that will be received.

#### 2.5.7. Outcome and Measurements

Consenting patients will be emailed a secure link containing the online preoperative screening tool (Section 2.4) during their visit to the surgical clinic, usually 4–6 weeks prior to their scheduled procedure. Non-responders will be sent reminder emails within 7–14 days to maximise the response rate. Participants will be included if they complete the screening tool between 1 and 12 weeks prior to their scheduled surgery.

All screening tool data will be collated, including the patient characteristics and time between survey and surgical procedure, to gather concise information regarding patient characteristics and feasibility.

#### 2.5.8. Sample Size Calculation

A minimum sample size of 200 patients is required to determine the correlation between the preoperative screening tool scores and postoperative complications (primary outcome), assuming a moderate effect size (r = 0.3), α = 0.05, and 80% power, while accounting for potential dropouts (30%) and multiple variables in the logistic regression analysis. However, we aim to recruit a larger sample to enable robust determination of risk thresholds for individual patient cohorts based on cancer type (e.g., colorectal, pancreatic, gastric), patient characteristics (e.g., age groups, comorbidity profiles), and surgical approaches.

#### 2.5.9. Surgical Outcomes

All outcomes will be independently extracted from the hospital electronic medical records by study personnel blinded to the patients’ preoperative status.

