#### 2.5.10. Primary Outcomes

Proportion of patients developing in-hospital postoperative complications: defined as any deviation from the normal postoperative course and classified according to the Clavien–Dindo Classification (CDC) [41].

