#### 2.5.11. Secondary Outcomes

Intensive Care Unit (ICU) length of stay (days);Hospital length of stay (days);All-cause perioperative mortality (up to 30 days from index surgery).

Other patient characteristics and surgical outcomes extracted will include age, gender, type of cancer, surgical procedure, surgical time, discharge destination, and hospital readmission within 30 days. Acceptability of the preoperative online screening tool and willingness to participate in non-routine preoperative interventions will also be measured.

Other outcomes will include the Comprehensive Complications Index (CCI) [42,43] and Days Alive and at Home within 30 days (DAH30) [44,45]. The Comprehensive Complications Index (CCI) uses complications graded with the CDC, where each CDC grade has a specific CCI score and weight of complication (wC), to provide an overall accumulating score between 0 (no complications) and 100 (death) [42]. CCI score can be generated using the freely available online tool at https://www.cci-calculator.com/ (accessed on 12 May 2024) or calculated using the following formula:
$$CCI=\frac{\sqrt{wCI+wC2\ldots +wCx}}{2}$$

DAH30 will be calculated using mortality and hospitalisation data from the date of the index surgery, as described in detail by Myles et al. [44].

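### Mortality to day 30, 30-day readmission and DAH30 rest on the hospital record alone, so deaths and admissions elsewhere after discharge may be missed

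*Protocol article*

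**What the plan says.** All references are to the protocol article.

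- **Source.** Section 2.5.9: "All outcomes will be independently extracted from the hospital electronic medical records". Section 2.5.1 on the follow-up period: "Patient data will be collected from the online screening tool and electronic medical records over this period".
- **Follow-up.** Section 2.5.1: patients "will be followed until 30 days post-operation". Recruitment is "at several national and international hospitals over a 12-month period".
- **Primary outcome.** Section 2.5.10: "Proportion of patients developing in-hospital postoperative complications".
- **30-day outcomes.** Section 2.5.11 lists as a secondary outcome "All-cause perioperative mortality (up to 30 days from index surgery". It also lists readmission within 30 days, and under other outcomes it says "DAH30 will be calculated using mortality and hospitalisation data from the date of the index surgery".
- **Timing of the online tool.** Section 2.5.7 includes patients who complete it between 1 and 12 weeks before surgery.

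The article does not mention contact with the patient or family after discharge, records from other hospitals, data linkage or a death register.

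**The concern.** The article fixes one source for every surgical outcome and then lists three outcomes that this source may not fully observe. Suppose a patient goes home on day 7, is admitted near home on day 12, or dies at home on day 20. Unless someone reports it, the operating hospital may hold no entry.

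Readmission, 30-day mortality and DAH30 are the measures that look past the index stay, because the primary outcome stops at discharge. If unseen events are taken as no event, readmission and mortality come out too low and DAH30 too high. The sites are in several countries, and their records may differ in how much they show of admissions and deaths elsewhere. The size of the error may then vary by site, and a site with narrower records would look better for that reason alone.

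**Working it through.** **1. Source against outcome.** The plan states no figure for completeness of capture, so there is none to reproduce. The check sets each outcome against the only source that could supply it. The online tool is completed before surgery and cannot record postoperative events, so that source is the hospital record.

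| Outcome | Where the event can occur | Covered by the hospital record? |
|---|---|---|
| In-hospital complications (primary) | Index stay | Yes |
| ICU and hospital length of stay (index) | Index stay | Yes |
| Death to day 30 | Anywhere | Only if it reaches the record |
| Readmission within 30 days | Any hospital | Only if it reaches the record |
| DAH30 | Built from deaths and hospital days | Only as far as the two rows above |

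**2. Possible size for readmission and death.** Input from the document: the minimum of 200 with 30% dropout (section 2.5.8), so 200 × 0.70 = 140 if all dropouts are lost to analysis. Assumed, not in the document: true readmission 10-15%, true 30-day mortality 2%, and 10-30% of events not visible in the record.

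Observed rate = true rate × (1 − share missed). Expected events among 140 are in brackets.

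| True rate | 10% missed | 20% missed | 30% missed |
|---|---|---|---|
| Readmission 10% (14.0) | 9.0% (12.6) | 8.0% (11.2) | 7.0% (9.8) |
| Readmission 12% (16.8) | 10.8% (15.1) | 9.6% (13.4) | 8.4% (11.8) |
| Readmission 15% (21.0) | 13.5% (18.9) | 12.0% (16.8) | 10.5% (14.7) |
| Death 2% (2.8) | 1.8% (2.5) | 1.6% (2.2) | 1.4% (2.0) |

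At 12%, a missed share of 20-30% loses 16.8 × 0.20 = 3.4 to 16.8 × 0.30 = 5.0 readmissions. The article aims for more than 200 patients. That raises the counts but leaves the rates unchanged.

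**3. Difference between sites.** Take two sites with the same true rate of 12%. One sees every readmission and the other misses 30%. They report 12.0% and 12% × 0.70 = 8.4%, a gap produced by the records alone.

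**4. DAH30.** Rise in the mean from missed readmissions = readmission rate × share missed × days per readmission. With 3 to 7 days per readmission (assumed), this runs from 0.10 × 0.10 × 3 = 0.03 to 0.15 × 0.30 × 7 = 0.32 days.

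For one patient the error can be large. Take discharge on day 8 and an unrecorded death at home on day 12. If the patient is taken as alive and at home, recorded DAH30 is 30 − 8 = 22. The article leaves the scoring of death to a cited source. If days before death count, the true value is 12 − 8 = 4 and the error is 18 days. If death scores 0, the error is 22 days.

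**5. Effect on the association.** Let the true risks in high-score and low-score patients be p1 and p0, and let a share m be missed in both groups. The observed risk ratio is p1(1 − m) / [p0(1 − m)] = p1/p0, which is unchanged. The odds ratio moves towards 1 only through the non-event terms. Equal capture therefore costs events and precision. Appreciable bias in the association needs capture that differs by risk group, or by site where sites also differ in risk.

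**The case against.** **The article never says the records are unlinked.** It does not say that each record is confined to one hospital, and some sites may see admissions and deaths elsewhere. This stands. The claim is that events may be missed, not that they will be.

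**No coding rule is stated.** A reader might infer that a patient with no entry is scored as alive, at home and not readmitted. The article does not say how unconfirmed 30-day status is coded, and section 2.5.12 promises a separate analysis plan that may settle it. This stands too, so the DAH30 example shows what would follow from such coding and does not describe the plan. An analysis plan cannot, however, recover events that were never collected.

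**A condensed article leaves such operational detail to the full protocol.** This is only partly right. The article is not silent on the source: section 2.5.9 names one and applies it to every outcome. That is a stated rule that does not match the outcome definitions.

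**Only lesser outcomes are touched.** This is correct. Of the affected measures, only 30-day mortality is a listed secondary outcome, and the sample size rests on the primary outcome.

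**Two stronger readings fail.** One is that the source rule contradicts the line "Acceptability of the preoperative online screening tool and willingness to participate in non-routine preoperative interventions will also be measured". It does not. The rule sits under the heading on surgical outcomes, these items are said to be measured separately, and section 2.5.1 names the online tool as a source. The other is that missed events must weaken the link with the preoperative score. That depends on differential capture, which the document neither shows nor rules out.

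**Conclusion.** The concern holds in a limited form. The named source may not capture post-discharge deaths and admissions that section 2.5.11 includes by definition. Mortality and readmission may be understated and DAH30 overstated, to an extent that may differ across national and international sites. The primary outcome and the index hospital and ICU stays are unaffected, so the main analysis is not in doubt.

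Under the assumed rates, observed readmission would be 7.0-9.0% for a true 10%, and 10.5-13.5% for a true 15%. Mean DAH30 would rise by about 0.03 to 0.32 days through missed readmissions. The average shift is small, but the error for a single missed death can be 18 to 22 days. All of these rest on assumed event rates and missed shares, and the DAH30 figures also on unseen patients being counted as at home. What the document itself establishes is the mismatch between source and definition.

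**What to change.** In section 2.5.9, keep the hospital record as a source for all surgical outcomes and add the following for the 30-day outcomes:

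- Send an automated REDCap email at day 30 to the address already used for the tool link (section 2.5.7). Ask about any hospital admission since discharge, its dates and current residence.
- Use linked admission or death data where a site already has them.
- Count an event if any source shows it. Code 30-day status as unknown, not event-free, when no source confirms it.
- If a site cannot do this, label its readmission, mortality and DAH30 as events recorded at the operating hospital only.

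The cost is one short survey and one consent line. Section 4 says that ethics approval and site authorisation are still to be sought, so both can go into those applications. The downside is some missing 30-day status, now visible. Non-response is likely to be informative, because patients who have died or are in hospital are less likely to answer. Completeness should therefore be reported by site, and patients of unknown status should not be assumed to resemble responders.
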